#### Implementation

One designated staff member will generate the allocation sequence using the randomization programme. After research investigators obtain informed consent from the subject, the staff will assign the patient to the determined group. The operator and other related investigators will be blinded just before surgery to perform proper management.

### Trial interventions

#### The LLH procedures

The LLH operative procedures will be completed by the same surgical team in each group led by two experienced board-certified surgeons. LLH and left lateral segmentectomy will be performed with the patient in the French position, with two experienced surgeons at each side (bilateral two chief surgeons) and a video laparoscope operator between the legs, which is different from the classic laparoscopic technique. Laparoscopic operations will be performed using 5 trocars. Common bile duct exploration (CBDE) will be performed in all patients with suspected stones in a dilated common bile duct (> 10 mm) using a choledochoscope, followed by T-tube placement if postoperative cholangiography is required [12] (Fig. 1).

**Fig. 1 Fig1:**
[figure not shown]
Surgical techniques for LLH

#### The procedures of OLH

OLH will be performed under general anaesthesia with the patient in the supine position. An inverted L-shaped incision will be performed. The left hepatic artery and left portal vein will be individually dissected, ligated, and divided. Then, the left bile duct and left hepatic vein will be ligated, divided, and closed after hepatic parenchymal resection. The CBDE will be the same as the LLH.

#### Conversion from LLH to OLH

Any incision used for reasons other than trocar placement or specimen extraction will be defined as a conversion. Patients allocated to LLH but converted to OLH will still be analysed in the LLH group, according to intention-to-treat principles.

### Blinding

In this trial, all assessors of the primary outcome (i.e. the ward doctor), the patients, and the adjudication committee will be blinded to the operation allocation. Directly after skin closure, while still under general anaesthesia, patients will receive a firmly taped, large 40 × 40 cm abdominal dressing to cover their incision(s) and therefore their treatment allocation (minimally invasive or open). This abdominal dressing will be removed when all criteria for functional recovery are met or earlier for medical reasons, such as suspicion of wound infection. If an earlier inspection is needed, attempts will be made to maintain patient blinding.

The success of blinding will be assessed using the blinding index as proposed by Bang et al. [23]. Both patients and ward doctors will be asked about the alleged treatment allocation based on five categories: (1) strongly believe it was LLH, (2) somewhat believe it was LLH, (3) somewhat believe it was OLH, (4) strongly believe it was OLH, and (5) do not know. Sensitivity analysis will be performed for the analysis of time to functional recovery.

### Type of trial

The trial is a prospective randomized interventional single-centre study comparing two parallel groups with a prospective registry to determine whether patients underwent LLS by laparoscopic surgery rather than open surgery with an enhanced recovery programme. The types of interventions by patients, nurses, and ward doctors (not the surgeons performing the operations) before postoperative day (POD) 3 will be blinded. However, patients who are randomized to receive open or laparoscopic liver resection are at risk, as explained earlier. In addition, there is another potential source of bias when randomly selecting patients with strong treatment preferences. When patients are not informed about their treatment allocation (POD 3), they may be resentful and feel demoralized if they do not receive their preferred treatment. Thus, their compliance may be poor. In contrast, patients receiving their preferred treatment may have above-average compliance. Thus, to capitalize on centres both with and without preference for laparoscopic liver surgery and to acquire an uninterrupted prospective series of patients, all nonrandomized patients undergoing LLS will be approached to participate in the prospective registry. Registration of these patients is imperative to guarantee a consecutive series of patients and because the absence of such a series may restrict the generalization of the results, as randomized participants may not, in fact, be representative [24].

Nonrandomized patients will be asked for permission to use their data. In doing so, they will be assigned to the OLH or LLH group of the prospective registry on the basis that this registry might increase the external validity of results obtained in the randomized study [15, 18, 25].

### ERAS programme

All patients will participate in the ERAS liver programme with standardized perioperative management. For the daily guidelines on the pre- and postoperative care of patients undergoing liver resection, see Fig. 2.

**Fig. 2 Fig2:**
[figure not shown]
ERAS programme. CVP, central venous pressure

### Withdrawal

Patients can withdraw from the trial at any time at their own request or at the request of their legal representative. Patients may be removed if, in the researchers’ opinion, continuing the trial may be detrimental to the patient’s health, if left hepatectomy is not performed due to a technical inability, or for other reasons. Every withdrawal will be recorded in the clinical report forms (CRFs) and in the patient’s medical case records. All examinations scheduled for the final trial day will be performed on all patients and documented. All data will be analysed according to the intention-to-treat (ITT) principle [26].

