### Secondary endpoints

The secondary outcomes are biliary leak [19], haemorrhage [20], posthepatectomy liver failure [21], wound infection, intra-abdominal fluid collection or abscess, relaparotomy, mortality, long-term abdominal wall hernias, hospital costs, residual stone rate and recurrence of calculus [22]. Existent ISGLS definitions will be used to ensure the comparability and generalizability of the results. Postoperative complications will be graded based on severity according to the Clavien–Dindo definition [27] (Tables 1 and 2).

**Table 1 Tab1:** Definition of the secondary endpoints

Secondary endpoint	Definition and assessment of outcomes
Operative time	Time from beginning to end of operation
Mortality	Death due to any cause until 90 days after the operation and the reason
Morbidity	Postoperative complications will be recorded until 90 days after operation. The severity of complications will be graded according to the Clavien–Dindo classification [27]
Blood loss	Total blood loss during the operation
Intraoperative blood transfusion	Massive haemorrhage with hemoglobin level < 7 g/dl or Hct < 22
Postoperative hospital stay	Time from the day of operation until discharge(days)
Post-hepatectomy haemorrhage	Evidence of blood loss from drains and/or nasogastric tube, based on ultrasonography, as defined by ISGPS (grade A, B, or C) [20]
Biliary leak	Bilirubin concentration in the drain fluid at least three times the serum bilirubin concentration as defined as ISGLS (grade A, B or C) [19]
Post-hepatectomy liver failure	The impaired ability of the liver to maintain its synthetic, excretory, and detoxifying functions, which are characterized by an increased international normalized ratio and concomitant hyperbilirubinemia (according to the normal limits of the local laboratory) on or after postoperative day 5 as defined as ISGLS (grade A, B, or C) [21]
Intraabdominal fluid collection	Collection of fluid measuring ≥ 3 cm associated with clinical or laboratory abnormalities
Pneumonia	Presence of a new infiltrate on chest X-ray, as well as following: body temperature > 38℃, abnormal elevation of WBC, or positive sputum, and requiring antibiotic treatment
Wound infection	Surgical site infection associated with laparotomy that develops during the initial hospital stay
Abdominal rupture	Dehiscence of abnormal closure with need for resuture of the laparotomy during the initial hospital stay

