### Data collection and patient follow-up

Data will be collected prospectively for all patients, including history, physical examination, laboratory data, pathologic examination, perioperative clinical information, and complications. Data will be collected via datasheets on paper and kept securely. Study subjects will complete the examinations at inclusion, 1 week after surgery, and 3, 6, 12, 24, and 36 months postoperatively. Follow-up will be conducted at 1 month postoperatively and then 3, 6, 12, 24, and 36 months postoperatively by telephone or as outpatients with liver function tests and abdominal ultrasonography for 3 years or until death. CT or MRCP will be performed in cases of suspected stone recurrence or cholangitis (Table 1). All handling cases will be managed by subject identification codes or anonymized registration numbers. The correspondence table of the anonymizing code and names and the consent form containing the names will be kept strictly in separate lockable document storage. All required parameters will be collected in an SPSS data file (SPSS version 25, IBM statistics, Chicago, IL, USA).

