#### Statistical analysis

The two-sided null hypothesis for the primary endpoint states that both study interventions will lead to a similar time to the LOS; the alternative hypothesis is that one intervention will perform better than the other. The null hypothesis will be tested by analysing the covariance while adjusting for age and the type of liver resection. A binary logistic regression will be applied to compare the time to functional recovery between groups after adjusting for other factors. Background characteristics and surgical outcome measures will be compared using chi-squared or Fisher’s exact tests for categorical data and two-tailed* t* tests or nonparametric Mann–Whitney *U* tests for continuous variables. Categorical data will be presented as the frequencies and group percentages, and continuous variables will be expressed as the means and standard deviations. The homogeneity of the two groups will be described by comparison of the demographic data and baseline values. All analyses will be performed on an ITT basis [17]. For the ITT analyses, the data will be processed for all trial patients in their randomized groups. A *P* value < 0.05 will be considered statistically significant. All statistical calculations will be performed using SPSS 22.0 (SPSS version 25, IBM statistics, Chicago, IL, USA).

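### The only test named that fits 36-month stone recurrence and hernia ignores unequal follow-up, and the final-trial-day rule for withdrawals is ambiguous

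*Protocol article*

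**What the plan says.** All references are to the protocol article.

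- **Secondary endpoints** lists long-term abdominal wall hernia, residual stones and recurrence of calculus. The recurrence row of Table 1 classes stones found within 3 months of hepatectomy as residual, so recurrence can only be counted after that.
- **Data collection and patient follow-up** schedules contacts at 1, 3, 6, 12, 24 and 36 months, "with liver function tests and abdominal ultrasonography for 3 years or until death".
- **Withdrawal** states: "Patients can withdraw from the trial at any time at their own request or at the request of their legal representative". Researchers may also remove patients. After requiring each withdrawal to be recorded, it says: "All examinations scheduled for the final trial day will be performed on all patients and documented".
- **Sample size calculation** expects 10% withdrawal and adds 18 patients, for a total of 190.
- **Statistical analysis** states: "Background characteristics and surgical outcome measures will be compared using chi-squared or Fisher’s exact tests for categorical data". On the analysis set it says: "For the ITT analyses, the data will be processed for all trial patients in their randomized groups". It names no time-to-event method.

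**The concern.** Follow-up length will differ between patients: some leave, some die, and the rest are seen to month 36. A chi-squared or Fisher's test needs a yes or no from each patient and makes no use of time. For a patient who leaves event-free at month 5, the named test offers no status between event and no event. A patient last imaged before month 3 cannot be a recurrence case at all under Table 1, yet belongs to the all-randomised denominator.

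If such patients were carried as event-free, both 36-month rates would be too low, and the arm that lost more patients would look better. The protocol gives some reason to expect unequal loss. Its Type of trial section warns of poor compliance among patients who do not get their preferred treatment. Patients learn their allocation after postoperative day 3, so nearly all of the 36 months follows disclosure.

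These outcomes matter to the trial. The Background of the abstract lists hernia and recurrence among the unproven advantages of laparoscopy, and the Discussion treats residual stones and recurrence as surgeons' main concerns.

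**Working it through.** **The protocol's own figure.** 86 per arm gives 2 × 86 = 172. Ten per cent of 172 is 17.2, rounded up to 18, and 172 + 18 = 190, as stated. (Dividing by 0.9 gives 191.1, or 192 in equal arms; the gap is immaterial here.) That is 95 randomised per arm.

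**Inputs for the illustration.** The 10% withdrawal is the protocol's. It gives no recurrence or hernia risk and no withdrawal split by arm, so those are assumptions.

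- p: true 36-month risk, assumed 15% in both arms (10% as an alternative).
- w: proportion of an arm lost to follow-up.
- f: share of the 36-month risk already accrued when a patient is lost. f = 0 means all loss precedes any event, the worst case.
- Scoring: lost patients stay in the denominator without an event. This is a supposition.

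**Formula.** Observed risk = p × [1 − w × (1 − f)].

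| p | Loss, arm A v arm B | f | Observed A v B | Difference (points) | Ratio A/B |
|---|---|---|---|---|---|
| 15% | 10% v 10% | 0 | 13.5% v 13.5% | 0 | 1.00 |
| 15% | 15% v 5% | 0 | 12.75% v 14.25% | 1.5 | 0.89 |
| 15% | 18% v 2% | 0 | 12.3% v 14.7% | 2.4 | 0.84 |
| 15% | 15% v 5% | 0.5 | 13.875% v 14.625% | 0.75 | 0.95 |
| 10% | 15% v 5% | 0 | 8.5% v 9.5% | 1.0 | 0.89 |

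For example, 0.15 × (1 − 0.15) = 0.1275 and 0.15 × (1 − 0.05) = 0.1425. The true difference is zero in every row. With f = 0 the ratio is (1 − w_A)/(1 − w_B) whatever p is, so equal loss leaves it at 1.

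**Cost with equal loss and a real effect.** With 95 per arm, an assumed hernia risk of 10% v 3% would read 9.0% v 2.7% after 10% loss in each arm; power falls from about 50% to 46%. For 20% v 5% it would read 18.0% v 4.5%, and power falls from about 88% to 84%.

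**Scale.** The standard error of a difference at 15% with 95 per arm is √(2 × 0.15 × 0.85 / 95) = 5.2 points. A 1.5-point shift is 0.015 × 95 = 1.4 patients.

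**The withdrawal sentence.** Two readings are open. If the examination is brought forward to the day of withdrawal, the last look may come long before these events arise. If it means month 36 for everyone, it cannot be guaranteed alongside the right to leave at any time. The text does not choose between them.

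**The case against.** The strongest reply is that the protocol never says how incomplete follow-up is scored. The all-randomised sentence concerns group assignment; exclusion, imputation or available-case analysis remain possible, and such rules are often left to an analysis plan, which is not shown. This stands: the absence of a missing-data rule is not the point, and a reader who infers that withdrawn patients will be counted as event-free goes beyond the text. What remains is that the one test named for such outcomes cannot use partial follow-up.

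A reader might also infer that withdrawn patients contribute a single early examination. The text does not support this. Nothing moves the final examination to the withdrawal date, and visits before withdrawal also supply data.

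Nor is it an error to keep patients who die event-free in the denominator. A cumulative incidence with death as a competing event does the same; without other censoring before month 36 it equals events divided by all randomised.

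The section speaks of surgical outcome measures and does not name hernia or recurrence. Applying the sentence to them is an inference, though no other named method fits.

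Finally, the unequal losses are assumed. The compliance warning concerns patients with strong preferences, many of whom would go to the registry, and poor compliance is not the same as loss. Unequal loss is therefore plausible but not documented. Even so, the shifts shown are well below one standard error.

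**Conclusion.** The concern holds in a limited form. For two outcomes followed to 36 months with 10% expected withdrawal, the only named test that fits takes no account of unequal follow-up, and the withdrawal sentence does not settle what is collected from patients who leave.

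The size is modest and conditional. If lost patients were kept as event-free, 10% loss per arm would lower each rate by at most a tenth of its value and leave the risk ratio unchanged. Bias between arms needs unequal loss: at 15% v 5%, a true null would read as a ratio of 0.89, or 1.12 with the arms reversed. These figures rest on assumed risks, assumed splits and loss before any event; loss halfway through the accrual of risk halves the shift. Only secondary endpoints are concerned, and the primary length-of-stay analysis is little affected. The change is still worth making because a better method is available on visits already scheduled.

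**What to change.** **Statistical analysis.** Analyse stone recurrence (counted after the 3-month residual-stone window) and abdominal wall hernia as time to first event by randomised arm. Censor at the last imaging or examination, treat death as a competing event, and report 36-month cumulative incidence by arm. Keep chi-squared or Fisher's exact tests for in-hospital and 90-day outcomes.

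**Withdrawal.** Replace the final-trial-day sentence. Patients who stop trial procedures stay in the existing follow-up schedule unless they also refuse follow-up; in that case the date and status of the last assessment are recorded.

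**Cost.** Wording in two sections and a standard survival analysis. No visits are added to the existing schedule. Intervals will be slightly wider and reported rates slightly higher than under a crude proportion that counts lost patients as event-free.

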### Primary endpoint

The primary outcome of this trial is the LOS. Only the researchers and surgical surgeons will know the true operation. A blinded ward doctor will decide whether the patient should be discharged.

### Secondary endpoints

The secondary outcomes are biliary leak [19], haemorrhage [20], posthepatectomy liver failure [21], wound infection, intra-abdominal fluid collection or abscess, relaparotomy, mortality, long-term abdominal wall hernias, hospital costs, residual stone rate and recurrence of calculus [22]. Existent ISGLS definitions will be used to ensure the comparability and generalizability of the results. Postoperative complications will be graded based on severity according to the Clavien–Dindo definition [27] (Tables 1 and 2).

**Table 1 Tab1:** Definition of the secondary endpoints

Secondary endpoint	Definition and assessment of outcomes
Operative time	Time from beginning to end of operation
Mortality	Death due to any cause until 90 days after the operation and the reason
Morbidity	Postoperative complications will be recorded until 90 days after operation. The severity of complications will be graded according to the Clavien–Dindo classification [27]
Blood loss	Total blood loss during the operation
Intraoperative blood transfusion	Massive haemorrhage with hemoglobin level < 7 g/dl or Hct < 22
Postoperative hospital stay	Time from the day of operation until discharge(days)
Post-hepatectomy haemorrhage	Evidence of blood loss from drains and/or nasogastric tube, based on ultrasonography, as defined by ISGPS (grade A, B, or C) [20]
Biliary leak	Bilirubin concentration in the drain fluid at least three times the serum bilirubin concentration as defined as ISGLS (grade A, B or C) [19]
Post-hepatectomy liver failure	The impaired ability of the liver to maintain its synthetic, excretory, and detoxifying functions, which are characterized by an increased international normalized ratio and concomitant hyperbilirubinemia (according to the normal limits of the local laboratory) on or after postoperative day 5 as defined as ISGLS (grade A, B, or C) [21]
Intraabdominal fluid collection	Collection of fluid measuring ≥ 3 cm associated with clinical or laboratory abnormalities
Pneumonia	Presence of a new infiltrate on chest X-ray, as well as following: body temperature > 38℃, abnormal elevation of WBC, or positive sputum, and requiring antibiotic treatment
Wound infection	Surgical site infection associated with laparotomy that develops during the initial hospital stay
Abdominal rupture	Dehiscence of abnormal closure with need for resuture of the laparotomy during the initial hospital stay
Total hospitalization expenses	Hospital costs from admission to discharge ($)
Recurrence of calculus	Calculi in the intrahepatic duct within 3 months after hepatectomy are defined as residual stones [22]

**Table 2 Tab2:** Severity grade according to the Clavien–Dindo definition [27]

Grade	Definition
I	Any deviation from the normal postoperative course without the need for pharmacological treatment or surgical, endoscopic, and radiological intervention
II	Requiring pharmacological treatment with drugs other than those allowed for grade I complications
III	Requiring surgical, endoscopic, or radiological intervention
IIIa	Intervention not under general anaesthesia
IIIb	Intervention under general anaesthesia
IV	Lifer-threatening complication. Requiring intensive care unit management
IVa	Single-organ dysfunction
IVb	Multiorgan dysfunction
V	Death of patient

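### Table 1 defines the intraoperative transfusion endpoint by a bleeding and laboratory state, so a patient transfused outside that state would not be counted

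*Protocol article*

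**What the plan says.** The Secondary endpoints section contains Table 1, titled "Definition of the secondary endpoints". Its right-hand column is headed "Definition and assessment of outcomes". One row is labelled "Intraoperative blood transfusion", and the full entry beside it is "Massive haemorrhage with hemoglobin level < 7 g/dl or Hct < 22".

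The entry does not mention blood being given, which product counts, or how much. No volume is attached to the word for severe bleeding, the haematocrit figure has no unit, and no time of measurement is stated.

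Intraoperative blood loss has its own row. The running text of the section lists secondary outcomes, beginning "The secondary outcomes are biliary leak [19], haemorrhage [20], posthepatectomy liver failure [21], wound infection, intra-abdominal fluid collection or abscess, relaparotomy, mortality", and transfusion is not in that list. It is also absent from the secondary outcomes in the Abstract. In the readable text, Table 1 is the only place where the endpoint is named or defined.

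**The concern.** The endpoint is named after an intervention, but the cell that defines it describes a patient's condition. The two need not coincide. A patient may receive blood without being in that condition, and a patient may be in it without receiving blood during the operation. Whoever codes the endpoint must choose between the label and the definition, and two assessors could code the same patient differently.

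What is at stake is the meaning of one reported rate. The Statistical analysis section plans chi-squared or Fisher's exact tests for categorical surgical outcomes, so this row would presumably be reported and compared by arm. A figure built on the printed rule would be presented as a transfusion rate without being one.

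This is not a detail that the article merely leaves to a fuller document. A definition is stated, and it does not measure the thing named.

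**Working it through.** No formula applies: the point does not depend on alpha, power, an effect size or a rate, and the plan gives no figure to reproduce. The check is logical.

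**Inputs**, all from Table 1:
- the row label, which names transfusion during the operation;
- the cell, which requires severe bleeding together with haemoglobin below 7 g/dl or haematocrit below 22;
- the table title and column heading, which present the cell as the outcome definition and not as treatment guidance.

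**Step 1. Cross the event with the criterion, taking the cell alone as the rule.**

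| | Criterion met | Criterion not met |
|---|---|---|
| Blood given during surgery | counted, correct | not counted, false negative |
| No blood given during surgery | counted, false positive | not counted, correct |

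**Step 2. Repeat with label and cell read together**, that is, transfusion given in the stated circumstance.

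| | Criterion met | Criterion not met |
|---|---|---|
| Blood given during surgery | counted, correct | not counted, false negative |
| No blood given during surgery | not counted, correct | not counted, correct |

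The false-positive cell disappears. The false-negative cell does not.

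**Step 3. Check whether the grammar matters.** The cell could be parsed so that the bleeding requirement applies to both laboratory values or only to haemoglobin. Under either parse, a patient transfused with haemoglobin of at least 7 g/dl and haematocrit of at least 22 is missed. How many more are missed because their bleeding is not judged massive depends on the parse.

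**Step 4. Ask when no patient would be misclassified.** Under the cell-alone reading, blood would have to be given during surgery exactly when the criterion is met. Under the combined reading, it would have to be given only when the criterion is met. No readable section says either. The ERAS figure is not shown and might contain a transfusion rule. Even so, a rule for giving blood would not make this row a record of blood given, unless adherence were complete.

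**Step 5. Try to size it.** The number misclassified needs the transfusion rate and the share of transfusions outside the criterion; under the cell-alone reading it also needs the share of patients who meet the criterion and are not transfused. The protocol gives none of these.

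**The case against.** The strongest reply is that the row label already supplies the event and its time window, and that the cell adds the circumstance. On that natural reading the endpoint is transfusion given for the stated indication, and a patient who receives no blood is not an event. This stands: the false-positive half cannot be asserted flatly. It does not remove the other half, because a patient transfused outside the indication is still not counted.

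A second reply is that this is a condensed article. Product, units and yes/no coding commonly sit in the full protocol or the case report form, and the data collection section says that perioperative data are gathered. It is fair that the absence of such detail is no finding. The point here is the definition that is printed.

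A third reply is that the outcome is peripheral. That is correct, and it limits the weight of the point.

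A reader might go further and infer that the recorded rate is too low by some stated fraction, that any difference between arms is diluted, or that haemoglobin is sampled unequally in laparoscopic and open surgery and so biases the comparison. The documents support none of these. They give no rates and no intraoperative sampling schedule. Dilution in proportion would require the same missed share in both arms and no false positives.

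**Conclusion.** The point holds as a minor defect of definition. As printed, the rule does not count a patient who is transfused during surgery without meeting the stated values. Where the bleeding requirement applies, it also leaves out a transfused patient whose bleeding is not judged massive. Only if the cell is read without its label does the rule also count a patient who meets the values and receives no blood.

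The size is unknown, and so is the direction of any effect on the comparison between arms. The conclusion assumes only that some transfusions may be given outside the stated criterion, which nothing in the readable text excludes. It does not require that this happens often.

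It would be wrong to infer that the trial's main result is threatened. The primary endpoint, its analysis of covariance and the sample size do not use this row.

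**What to change.** Redefine the Table 1 row as blood product actually given between the start and the end of the operation, recorded as yes/no with the amount. State which products count; that choice is the sponsor's.

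If the haemoglobin and haematocrit values are meant as the indication for transfusion, state them separately from the outcome definition, for example with the description of perioperative care. No view is taken on the values or on when blood should be given.

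The cost is one table row, plus a check that the datasheets record whether blood was given and how much. Sample size, randomization and the primary analysis do not change.
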